The treatable trait success story of chronic asthma certainly makes a case for the reappraisal of our approach to acute asthma.^6 7 43^ Is it time for precision medicine to attack the problem of asthma attacks? A worthwhile question, considering that corticosteroid toxicities appear after the lifetime equivalent of only four bursts (≥1000 mg cumulative dose) of prednisone—that is, four severe asthma attacks^44^—and the increasing levels of resistance to antibiotics observed, mainly due to inadequate prescriptions.^7 29^ Biomarker-guided management could avoid harm to individual patients and society stemming from the inappropriate use of OCs and/or antibiotics due to overuse or without proper consideration of their potential risks and side effects.^44 45^ Simply stated, corticosteroid and antibiotic stewardship can and should be assisted by acute POC testing.

Based on previous knowledge from chronic stable asthma and reports that asthma attacks are heterogeneous events, we hypothesise that treatment responses to OCs in acute asthma vary according to the underlying inflammatory phenotype. Specifically, we speculate that events identified by raised BEC and/or FeNO benefit most from OCs and that events presenting with low type 2 biomarkers have a lesser objective clinical and biological anti-inflammatory response but perhaps higher rates of airway infection or dysfunction. If this proves to be the case, we will be in a solid position to move forward with a randomised clinical trial comparing biomarker-directed OC use with the current ‘one-size-fits-all’ approach. An important secondary hypothesis of our study is that POC inflammatory and microbiological assessments in acute asthma are possible, acceptable and reliable. The ramifications of such findings would be to plan a clinical trial assessing biomarker-guided asthma attack management in primary care.

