### Outcome measures

#### Primary outcome

Change in the FEV_1_ between visits, with particular emphasis on a comparison based on the presence or absence of type 2 inflammatory events within the patient cohort. Specifically, we will classify type 2 high events on the basis of visit 1 BEC ≥0.15×10^9^ cells/L and/or FeNO ≥25 ppb.

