#### Exploratory outcomes

The continuous association between baseline biomarkers (BEC and FeNO) and changes in symptom scores, sputum inflammometry, additional lung physiology parameters (impulse oscillometry), inflammatory mediators (type 2 cytokines, chemokines, alarmins, eosinophils) and microbiome diversity across different immune compartments (nasal epithelium, induced sputum, serum, urine).Comparative agreement and reliability of gold-standard BEC (hospital laboratory) versus POC test (Sight OLO).An appraisal of POC biomarkers using patient satisfaction scores and primary care physician surveys.A sensitivity analysis on all of the above assessing how sex at birth, gender (self-identified: female, male, other specify) and race (self-identified)^59^ influence treatment responses.

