Patient satisfaction scores, physician surveys and the percentage of tests completed during the home monitoring period will be analysed descriptively. An intraclass correlation coefficient (two-way mixed model for absolute agreement, single measures) plus Bland-Altmann fixed bias estimate for gold standard (venous BEC performed in the laboratory) versus POC (capillary BEC via SightDx OLO) will be computed with 95% CIs.

In both primary and secondary outcomes, we will explore how treatment response to OCs may be influenced by sex, gender and diversity by conducting univariable and multivariable sensitivity analyses on those factors while also controlling for the type 2 inflammatory status. We will also perform a sensitivity analysis, disaggregating all statistical outputs by sex. Results will be presented using interaction plots.

All statistics will be analysed with a two-sided α of 0.05 and, when multiple inflammatory mediators are tested, by controlling for a false discovery rate <0.05.^60^ Statistical analyses will be performed with R V.4.1.2 (R Foundation) and GraphPad Prism (GraphPad Software, USA).

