PRISMA (Phenotyping the Responses to Systemic Corticosteroids in the Management of Asthma Attacks) Study offers a distinctive and comprehensive perspective in asthma exacerbation research compared with the studies above, as it stands out by exploring the vital and often less-understood components of asthma exacerbation: their response to standard medications, the utility of BEC and FeNO in acute settings, and the potential role of microbial infections in exacerbation dynamics. PRISMA can also be viewed as instrumental in participating and/or launching further studies about asthma attacks—a new and exciting frontier for biological therapies (eg, BeNReX (NCT04102800134), ABRA (NCT04098718135)).

If the POC test results prove reliable and are also acceptable to patients and their primary care providers, the table will be set for a placebo-controlled trial, such as being done in chronic obstructive pulmonary disease.^64–66^

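### The planned agreement statistics for point-of-care eosinophils, an ICC and a mean bias, do not show individual error or whether patients fall on the same side of the 0.15×10⁹/L cut-off

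*Protocol article*

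**What the plan says.** The Statistical analyses section sets out the comparison of laboratory and POC eosinophil counts in one sentence. It names two statistics:

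- "An intraclass correlation coefficient (two-way mixed model for absolute agreement, single measures";
- "Bland-Altmann fixed bias estimate for gold standard (venous BEC performed in the laboratory) versus POC".

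Precision is covered by "capillary BEC via SightDx OLO) will be computed with 95% CIs". The article does not mention limits of agreement, any measure of concordance at a cut-off, or a criterion for calling the device reliable.

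The Primary outcome section defines a type 2 high event by "visit 1 BEC ≥0.15×10^9^ cells/L and/or FeNO ≥25 ppb". Exploratory outcomes lists "Comparative agreement and reliability of gold-standard BEC (hospital laboratory) versus POC test (Sight OLO". The Introduction gives the topic more weight, as an important secondary hypothesis that "POC inflammatory and microbiological assessments in acute asthma are possible, acceptable and reliable". The Discussion links the result to a later placebo-controlled trial with the condition "If the POC test results prove reliable and are also acceptable to patients and their primary care providers".

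**The concern.** Each named statistic answers a narrower question than whether the device can be relied on.

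- **ICC.** It compares measurement error with the variation between patients. Eosinophil counts are usually right-skewed, so a few high counts can raise the ICC while readings near 0.15 remain imprecise.
- **Mean bias.** It averages signed differences, so over-reading and under-reading cancel. A bias of zero is compatible with any amount of individual error.

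BEC defines type 2 status as a yes/no label at 0.15×10⁹/L, and a trial of biomarker-guided treatment would presumably act on such a label. What matters for that use is the error of a single reading and the share of patients whose label changes with the device. The plan could be followed to the letter, and the device called reliable, with neither quantity reported.

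**Working it through.** **Inputs from the article.** Cut-off 0.15×10⁹/L (Primary outcome). The two statistics (Statistical analyses). About 50 confirmed patients (Sample size), with laboratory and POC counts both scheduled at days 0 and 7 (Table 1). The article states no numerical target for the agreement analysis, so there is no figure of its own to reproduce.

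**Assumptions, because the documents are silent.** Laboratory count X is log-normal with median M = 0.15–0.30 and log SD s = 0.7–0.9. POC count Y = X·E, where E is log-normal with mean 1 (zero bias) and CV c = 10%, 20% or 30%. Let t² = ln(1 + c²).

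**Formulas.**

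- Mean bias = 0 by construction.
- ICC (absolute agreement, single measures) = Var(X) / [Var(X) + Var(Y−X)/2] = (e^{s²} − 1) / [(e^{s²} − 1) + e^{s²}c²/2].
- Discordance at 0.15 = Φ(a) + Φ(b) − 2Φ₂(a, b; ρ), with a = ln(0.15/M)/s, b = [ln(0.15/M) + t²/2]/√(s² + t²) and ρ = s/√(s² + t²).
- 95% ratio limits = exp(−t²/2 ± 1.96t).

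**One case in full (M = 0.20, s = 0.7, c = 0.30).** e^{0.49} = 1.632, so ICC = 0.632/(0.632 + 1.632 × 0.045) = 0.90. t² = ln 1.09 = 0.086, a = −0.288/0.7 = −0.411, b = (−0.288 + 0.043)/0.759 = −0.322, ρ = 0.922. Discordance is 12.1%, with sensitivity 88% and specificity 87% against the laboratory count.

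**Across the assumed range.**

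| Error CV | Mean bias | ICC | Discordant at 0.15 | 95% ratio limits, POC/laboratory |
|---|---|---|---|---|
| 10% | 0 | about 0.99 | 2.6–4.5% | 0.82 to 1.21 |
| 20% | 0 | 0.95–0.97 | 5.3–8.8% | 0.67 to 1.45 |
| 30% | 0 | 0.90–0.93 | 7.9–12.8% | 0.54 to 1.70 |

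The bias column cannot tell the rows apart. The ICC moves little, while the last two columns change materially.

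**Sensitivity to the error model.** Suppose the error has a constant SD of 0.05×10⁹/L, with M = 0.25 and s = 0.8. The ICC is then 0.989 and the bias 0.000, yet 10.2% are discordant: 6.8% of true highs are missed and 19.7% of true lows are called high. An ICC of 0.99 can therefore accompany 3–5% discordance under one error model and 10% under another. Over a wider set of assumptions (median 0.15–0.40, log SD 0.6–1.0), with the ICC held at 0.90–0.98, discordance ran from 1.7% to 13.3% for proportional error and from 5.6% to 27% for constant error.

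**Composite status.** A patient with FeNO ≥25 ppb is type 2 high whatever the eosinophil count. If a share f has high FeNO independently of BEC, composite discordance = BEC discordance × (1 − f). With f = 0.5 (an assumption), the 30% row becomes about 4.0–6.4%.

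**Precision with 50 pairs.** Five discordant pairs of 50 give 10%, exact 95% CI 3.3% to 21.8%. Each limit of agreement has a 95% CI of about ±2.01 × √(1/50 + 1.96²/98) = ±0.49 SD of the differences.

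**The case against.** The ICC form and the mean bias are legitimate choices, and nothing in the article rules out further output from the same pairs. An article condenses a fuller plan, and the outcome is exploratory. The Sample size section already says that such analyses are likely underpowered and that significant findings need confirmation. BEC is also used as a continuous variable in the exploratory models, where an ICC is relevant.

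Much of this stands and limits how serious the point is. It does not remove it. The article specifies the ICC down to model, agreement type and unit, and then takes only the fixed bias from the Bland-Altman method. That is a choice of statistics rather than a detail left open. The power caveat does not help either, since more patients would not make an ICC or a mean bias show individual error.

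A reader might infer more than the documents support:

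- **That about one patient in ten will be misclassified.** This figure rests on an assumed distribution and device error. Under proportional error it belongs to the 30% CV; at 10% it is 3–5%.
- **That the limits of agreement exceed the cut-off itself.** At median 0.20 and CV 30%, raw limits are about ±0.19 to ±0.26, but high counts that are in no doubt inflate them. At a count of 0.15 the spread is about 1.96 × 0.30 × 0.15 = ±0.09.
- **That reliability is a formal gate to the next trial.** The link is a Discussion sentence with no threshold or decision rule.
- **That the primary comparison or treatment in this study is affected.** The article says "we will classify type 2 high events on the basis of visit 1 BEC" and calls the venous count the gold standard. If that count sets the groups, POC error cannot reach the FEV₁ result. Corticosteroids are given here as standard care, not by biomarker.

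**Conclusion.** The point holds as a weakness in the planned POC agreement analysis. The two named statistics can both look excellent without revealing individual error or agreement on the 0.15×10⁹/L label. What is at stake is the exploratory conclusion on POC reliability and its use in planning the next trial. The primary FEV₁ comparison is not at stake if venous BEC defines the groups.

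The size cannot be fixed from the documents. Under log-normal counts and unbiased proportional error, discordance is roughly 3–5%, 5–9% and 8–13% at error CVs of 10%, 20% and 30%. Other error models widen this range, and composite status is affected less. These figures show what could go unseen; they do not predict this device's performance. The change is worth making because it is nearly free, but it is not critical to the trial.

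**What to change.** Keep the ICC and the mean bias, and pre-specify two additions:

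1. **95% limits of agreement with CIs on the log (ratio) scale**, since error is likely to grow with the count. State in advance how zero counts are handled, because they have no logarithm.
2. **A cross-classification at 0.15×10⁹/L on the visit 1 pairs**, the visit that defines type 2 status. Report percent agreement, kappa, and sensitivity and specificity against venous BEC. Give exact CIs for the proportions and a CI for kappa.

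State that the POC reliability conclusion will rest on these as well as on the ICC and bias. It would help to show the same table for the composite BEC and/or FeNO status.

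The cost is a few lines of analysis on pairs already scheduled, with no extra visits or samples. The drawback is wide intervals with about 50 pairs (3.3% to 21.8% around 5 of 50), which is uncertainty that a pilot should pass on to the next trial's planning.

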### Sample size

For our primary analysis, assuming a two-sided α error of 0.05, a T2:non-T2 event ratio of 1:1 and a mean±SD population difference in δ FEV_1_ of 10±10%, n=46 will provide 90% of power to detect the difference in our primary outcome on an unpaired two-sample t-test. According to a recent Canadian study that assessed the proportion of randomly selected adults with physician-diagnosed asthma who fulfil objective criteria to confirm the diagnosis of asthma, 18.3% of participants reporting a severe asthma attack in the past year (11 of 60) did not have asthma confirmed.^61^ We thus conservatively estimate that 20% of patients recruited will not count towards the n=50 needed for the primary analysis.

Including a cohort of 12 healthy control participants, each assessed during a single visit, is intended to enhance our ability to relativise demographics, lung function and inflammatory measurements observed in the study. Recruitment will continue until the target number of confirmed asthmatics and healthy controls has completed the study.

We acknowledge that the secondary and exploratory analyses will likely be underpowered and view these as exploratory but feasible within the proposed timeline of a pilot study serving to plan further clinical trials. Any significant finding for secondary and exploratory outcomes will require further confirmatory studies to support them.^62^

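### Neither stated sex analysis estimates whether the type 2 high-versus-low contrast differs between the sexes, although sex-split outputs shown as interaction plots invite that reading

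*Protocol article*

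**What the plan says.** The Exploratory outcomes list ends with "A sensitivity analysis on all of the above assessing how sex at birth, gender" and race affect treatment responses. The Statistical analyses section applies this to the primary and secondary outcomes in two ways:

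- **Adjusted models.** The plan describes "conducting univariable and multivariable sensitivity analyses on those factors while also controlling for the type 2 inflammatory status".
- **Split outputs.** "We will also perform a sensitivity analysis, disaggregating all statistical outputs by sex. Results will be presented using interaction plots".

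The same section defines the tests that would be split: an unpaired t-test of change in FEV1 and in ACQ-5 by type 2 status, and a chi-square test of the MCID proportions by type 2 status. It also states: "All statistics will be analysed with a two-sided α of 0.05". No type 2 by sex product term, interaction estimate or interaction test is mentioned.

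The Sample size section describes the secondary and exploratory analyses as probably underpowered and says that any significant result from them needs confirmation.

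**The concern.** Three questions about sex can be asked here, and they have different null hypotheses.

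1. **Does mean response differ by sex, at a given type 2 status?** The sex coefficient in a model with sex and type 2 status answers this. Without a product term, that model assumes one type 2 effect common to both sexes.
2. **Is there a type 2 effect in women, and is there one in men?** The sex-split tests answer these as two separate questions.
3. **Is the type 2 effect the same in both sexes?** Neither stated analysis estimates this. It needs the difference between the two sex-specific contrasts, with its standard error.

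A type 2 contrast shown separately for each sex, as an interaction plot, leads the reader to the third question. With no matching estimate, the evidence to hand would be two p-values, each from about half the patients. Significance in one sex and not the other can then be taken for a sex-specific biomarker effect when it reflects only reduced power. The Abstract lists sex and gender variability in response among the exploratory aims, and the study is meant to inform a randomised trial, so such a reading could be carried forward.

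**Working it through.** **Inputs from the protocol.** Two-sided α of 0.05 (Statistical analyses); "a T2:non-T2 event ratio of 1:1", "population difference in δ FEV_1_ of 10±10"% and "n=46 will provide 90% of power to detect the difference in our primary outcome on an unpaired two-sample t-test" (Sample size). The target is 50 confirmed patients: "20% of patients recruited will not count towards the n=50 needed for the primary analysis". The Discussion puts type 2 high events at about 80% in severe asthma and says the proportion in milder disease is unknown.

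**Assumptions.** The protocol gives no sex split, so 50 to 70% in one sex is assumed. The type 2 high share is varied from 50 to 80%. FEV1 change is taken as normal with SD 10.

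**Step 1: reproduce the plan's figure.** With d = 10/10 = 1, the normal approximation gives 22 per group, or 44 in total. Noncentral-t power is 90.0% at 22 per group, 91.2% at 23 per group (46) and 93.4% at 25 per group (50). The stated 46 is reproduced to within two patients.

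**Step 2: power within one sex.** At n=50 with equal splits, each sex has 12.5 patients per type 2 group.

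- SE = 10 × √(1/12.5 + 1/12.5) = 4.0
- Noncentrality = 10/4.0 = 2.5 on 23 df, giving power 66.8%
- At n=46 the power is 62.8%

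**Step 3: chance that exactly one sex is significant when the true contrast is the same in both.** The sexes are independent samples, so P = pF(1 − pM) + pM(1 − pF).

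- n=50, equal splits: 2 × 0.668 × 0.332 = 44%
- n=46, equal splits: 2 × 0.628 × 0.372 = 47%
- A simulation of 40,000 studies gave 44.6% and 46.8%
- n=50, 70% in one sex, 80% type 2 high: 0.632 × 0.700 + 0.300 × 0.368 = 55%
- Highest in the range (n=46, 70% in one sex, 65% type 2 high): 0.745 × 0.630 + 0.370 × 0.255 = 56%

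**Step 4: dependence on the true contrast (n=50, equal splits).**

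| True contrast, both sexes | Power in each sex | Exactly one sex p<0.05 |
|---|---|---|
| 0 | 5.0% | 9.5% |
| 2.5 | 9.2% | 17% |
| 5 | 22% | 35% |
| 7.5 | 44% | 49% |
| 10 | 67% | 44% |
| 12.5 | 85% | 26% |
| 15 | 95% | 10% |

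**Step 5: direction.** At a contrast of 10, one sex's estimate has the wrong sign with probability Φ(−2.5) = 0.0062. Estimates of opposite sign therefore occur in 2 × 0.0062 × 0.9938 = 1.2% of studies.

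**Step 6: what an interaction term would deliver.** SE = 10 × √(sum of 1/n over the four sex-by-type-2 cells), with N − 4 df. Its false-positive rate is 5% when the contrasts are equal.

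- n=50, equal cells: SE = 10 × √(4/12.5) = 5.66; 95% half-width = 2.013 × 5.66 = 11.4 points. Power is 41% for a 10-point difference between contrasts and 14% for a 5-point difference; the difference detectable with 80% power is about 16 points.
- n=46, equal cells: SE 5.90, half-width 11.9, power 38% and 13%.
- Over the assumed ranges: half-width 11.4 to 16.2 points, power for a 10-point difference 23 to 41%, detectable difference 16 to 23 points.

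**The case against.** The protocol's written question is how sex, gender and diversity influence response to oral corticosteroids. Nowhere does it say in words that it will judge whether sex changes the type 2 contrast. Sex as a main effect, adjusted for type 2 status, is a coherent analysis of the written question. A reader might infer that the plan cannot answer its own question about sex; the documents do not support that.

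Nor do they support the inference that an interaction has been ruled out. The article is condensed, an analysis plan not shown may specify the term, and interaction plots fit naturally with a model that contains one. The protocol also does not say that significance in one sex only will be read as a sex difference. Disaggregation can be plain reporting.

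A reader might also infer that the sexes will disagree about half the time whenever there is no sex difference. That is too general. It holds for crossing p=0.05 and for true contrasts of roughly 7 to 10 points; the direction of the estimates almost never disagrees at the planning effect.

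Finally, these analyses are labelled exploratory, underpowered and in need of confirmation, and no sex-specific decision for the later trial is described. The proposed term would itself be imprecise.

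All of this stands and limits the priority. It does not remove the point. The plan does commit to splitting every output by sex and to interaction plots, under a blanket α of 0.05, without naming the one estimate that would support a comparison between the sexes. The caution about underpowered analyses guards against trusting a single positive result. It does not guard against misreading a significant result beside a non-significant one, a pattern that low power itself produces.

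**Conclusion.** The point holds in a limited form. The adjusted sex coefficient addresses mean response by sex. Neither stated analysis estimates whether the type 2 contrast differs by sex, which is the inference that the split outputs and interaction plots invite.

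The 44 to 56% chance of a significance split rests on the protocol's planning effect being true and equal in both sexes, on n=46 to 50, and on the assumed sex and type 2 shares. Since 10 points is the effect the study is designed around, the artefact is common just where the main hypothesis is right, but it is not a general rate. The consequence is confined to exploratory reporting, and the priority is optional to minor.

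**What to change.** In the Statistical analyses section, for change in FEV1 and in ACQ-5:

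- Fit one model in the confirmed patients with type 2 status, sex and their product.
- Report the interaction estimate with its 95% CI, and make it the only basis for any statement that sex modifies the type 2 contrast.
- Draw the interaction plots from that model.
- Give the sex-specific type 2 contrasts as estimates with CIs, and state that nothing will be concluded from significance in one sex and not the other.
- Keep the existing adjusted sex coefficient for the separate question of mean response by sex.

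If the full analysis plan already contains this term, a sentence in the protocol saying so is enough.

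The cost is one extra term in exploratory models and a few sentences; no new data are needed. The drawback is imprecision. For FEV1 the half-width of about 11 to 16 points exceeds the 10-point planning effect, so the result will often be that modification by sex is not determined.
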